### 3. Study Objectives

The primary objective of the study is to test the hypothesis that the thrombolytic tenecteplase (TNK, 0.25mg/kg) administered within 24 hours after symptom onset, is superior to current best practice (alteplase, rtPA, 0.9mg/kg or standard care/no lysis) in achieving excellent functional outcome or return to the premorbid modified Rankin Scale at 90 days in acute ischemic stroke patients with a large vessel occlusion and a significant volume of penumbral tissue on multimodal CT or MRI.

The primary hypothesis for ETERNAL LVO is that patients treated with 0.25mg/kg tenecteplase will have a greater proportion of Modified Rankin Scale (mRS) 0-1 (no disability) or return to baseline mRS (if baseline premorbid mRS =2) at 3 months compared to those treated with standard of care (0.9mg/kg alteplase or placebo).

### 4. Study Design

The study will be a prospective, randomised, open-label, blinded endpoint (PROBE), phase 3, parallel group, superiority trial with covariate-adjusted 1:1 randomisation, and adaptive sample size re-estimation in ischemic stroke patients with large vessel occlusion presenting to hospital within 24 hours of symptom onset (or last known well within 24 hours). Patients will be randomised to treatment with either standard of care (no intravenous thrombolytic treatment or intravenous alteplase 0.9mg/kg at the investigators discretion) or intravenous tenecteplase (0.25mg/kg). A covariate-adjusted randomisation procedure will be used to minimise imbalances for the following covariates: clinician intention to treat with alteplase or no thrombolysis if randomised to standard of care arm, age, NIHSS, premorbid mRS, site of Large Vessel Occlusion (Intracranial ICA and M1 vs extracranial ICA and M2, with tandem ICA occlusions to be considered intracranial for the purpose of covariate adjustment), and onset-to-randomisation time (less than 4.5h, 4.5-12h and 12-24h, where wake-up stroke/uncertain onset is 'last seen well within last 24 hours').

### 5. Study Population

The ETERNAL LVO trial will include patients with acute hemispheric ischaemic stroke, who are  $\geq 18$  years of age and are eligible for standard intravenous therapy within 24 hours of stroke onset or last known well within 24 hours, who have a large vessel occlusion. In addition to standard thrombolysis eligibility criteria, patients will be assessed for the presence of salvageable tissue without a large ischaemic core on CTP or MRI. Those that are shown by CTP/MRI to have a penumbral volume of greater than 15 mLs, an ischemic core volume of less than or equal to 70 mL, and a 'mismatch ratio' where the ratio of the perfusion lesion volume compared to the ischemic core volume is  $> 1.8$  measured using MISTar software. Large vessel occlusion on pre-randomisation CTA/MRA is *also* a requirement for inclusion into the study.

## 6. Number of Subjects

The sample size for the ETERNAL LVO study is estimated to be 370 per treatment arm (740 total). Adaptive sample size re-estimation using the Mehta and Pocock promising zone method will be used at n=592 (80% of estimated sample size).

Adaptive increase in sample size will be performed if the result of the interim analysis using data from the first 592 patients is promising. The maximum sample size is capped at 1000 patients.

This sample size is to be achieved through recruitment in Australia, New Zealand, Canada, Taiwan, Korea Germany, Spain, Belgium, Sweden and the United Kingdom at between 50 and 75 selected centres. Many of centres that are primary stroke centres with thrombectomy capability (i.e. 'drip and ship sites). Some of the primary stroke centres will include telestroke sites across Australia and Germany. Other countries may be added.

### 6.1 Inclusion Criteria

- Patients presenting with acute hemispheric ischaemic stroke with onset (or the time they last known to be well) within 24 hours.
- Patient's age is  $\geq 18$  years.
- Premorbid mRS  $< 3$ , with a concurrent assessment of whether the patient was able, immediately prior to the stroke, to: 1) Drive, or (if never drives) perform own Domestic duties, and 2) Shop for themselves, and 3) Bank/do their own finances (i.e. Drive/Domestic, Bank, Shop = DBS +ve). Need to be DBS +ve to be study eligible.
- Presence of a vessel occlusion on CTA or MRA. LVO will be defined as 'potentially retrievable' thrombus at one or more of the following sites: extracranial and/or intracranial internal carotid (ICA), middle cerebral artery (MCA) first segment (M1) and/or proximal middle cerebral artery second segment (M2).
- Presence of 'target mismatch' on perfusion CT (CTP) or diffusion-perfusion MRI as processed by MISTar. Mismatch is defined as an ischaemic core of  $< 70\text{mL}$ , penumbra of  $> 15\text{mL}$  and an ischemic core to perfusion lesion ratio of  $> 1.8$ .

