|                            | 
have met the CT perfusion defined mismatch criteria (perfusion lesion >15mL, mismatch ratio>1.5 and a baseline ischemic core <70mL)
 
Patients will be randomized to treatment with either standard of care (no intravenous thrombolytic treatment or intravenous alteplase 0.9mg/kg) or intravenous tenecteplase (0.25mg/kg), using an adaptive covariate adjusted randomisation procedure to minimise imbalance on the following covariates: clinician intention to treat with alteplase or no thrombolysis treatment if randomised to standard of care, age, NIHSS, premorbid mRS, site of Large Vessel Occlusion site (Intracranial ICA and/or M1 vs extracranial ICA and/or M2, with tandem ICA occlusions to be considered intracranial for the purpose of covariate adjustment), and onset-to-randomization time (with bins for: 0-4.5 hours, 4.5-12 hours and ≥12 hours, where wake-up stroke/uncertain onset is 'last seen well within last 24 hours').
                                                                                                                                                                                                                                                                                                                                                                                                                                                                                                                                                       |

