|                            | 
 
• Premorbid mRS <3, with a concurrent assessment of whether the patient was able, immediately prior to the stroke, to: 1) Drive, or (if never drives) perform own Domestic duties, and 2) Shop for themselves, and 3) Bank/do their own finances (i.e. Drive/Domestic, Bank, Shop = DBS +ve). Need to be DBS +ve to be study eligible.
 
• Presence of a large vessel occlusion on CTA or MRA. LVO will be defined as 'potentially retrievable' thrombus at one or more of the following sites: extracranial or intracranial internal carotid (ICA), middle cerebral artery (MCA) first segment (M1) or proximal middle cerebral artery second segment (M2). Presence of 'target mismatch' on perfusion CT (CTP) or diffusion-perfusion MRI as processed by MISTar. Mismatch is defined as an ischaemic core of <70mL, penumbra of >15mL, and an ischemic core to perfusion lesion ratio of >1.8.
 
                                                                                                                                                                                                                                                                                                                                                                                                                                                                                                                                                                                                                                                                                                                                     |

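### The target-mismatch criterion carries two ratio cut-offs and two volume rules, and both inclusion lists print the ratio in a direction that cannot be met

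*Protocol*

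**What the plan says.** The criterion appears in four places in the current protocol text.

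- **Synopsis, Study design.** The perfusion lesion must exceed 15 mL, with "mismatch ratio>1.5 and a baseline ischemic core" below 70 mL. The direction of the ratio is not spelled out.
- **Synopsis, Inclusion criteria.** Core below 70 mL, penumbra above 15 mL, and "an ischemic core to perfusion lesion ratio of >1.8".
- **Section 5, Study Population.** A "penumbral volume of greater than 15 mLs", "an ischemic core volume of less than or equal to 70 mL", and a mismatch ratio in which "the ratio of the perfusion lesion volume compared to the ischemic core volume is" above 1.8.
- **Section 6.1, Inclusion Criteria.** The sentence beginning "Mismatch is defined as an ischaemic core of" sets core below 70 mL, penumbra above 15 mL, and "an ischemic core to perfusion lesion ratio of" more than 1.8.

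Section 7.1 says that patients are assessed against the inclusion and exclusion criteria and that centres process the images in MIStar to determine eligibility. It does not say which thresholds the software applies.

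**The concern.** The primary hypothesis concerns patients with a large vessel occlusion and a significant volume of penumbra, and this criterion is what turns that phrase into a rule. Three of its elements conflict materially: the ratio cut-off (1.5 or 1.8), the volume that must exceed 15 mL (whole perfusion lesion or penumbra), and the direction of the ratio. The synopsis contradicts itself on all three if its design text intends the usual lesion-to-core direction.

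Eligibility is judged locally at 50 to 75 centres (section 6). If centres work from different parts of the document, patients near the boundaries could be enrolled at one and refused at another. A monitor checking eligibility has no single rule to check against. The exclusion criterion in section 6.2 on early ischaemic change that invalidates the mismatch criteria depends on the same unsettled definition.

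**Working it through.** **Inputs.** The thresholds are those listed above. Section 2 describes core as irreversibly damaged tissue and penumbra as salvageable ischaemic tissue, but gives no formula. I take perfusion lesion L = core C + penumbra P. I read the synopsis design ratio as L/C, the direction defined in section 5. The plan states no figure of its own to reproduce on this point.

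**1. The ratio as printed in section 6.1 and the synopsis inclusion list.**

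C/L = C/(C + P). With C < 70 mL and P > 15 mL, C/L < 70/(70 + 15) = 70/85 = 0.82.

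A value above 1.8 is out of reach. Even without the formula, a core lying inside the perfusion lesion gives C/L ≤ 1. A numerical grid in 0.5 mL steps (core 0 to 69.5 mL, lesion 0.5 to 399.5 mL) agrees. Of 97,930 grid points with C < 70 and P > 15, none has C/L > 1.8 (maximum 0.818), and 93,809 have L/C > 1.8. These are grid points, not an estimate of patients.

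**2. The two cut-offs and two volume rules, with the ratio taken as L/C.**

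- Section 5: L/C > 1.8 means P > 0.8C. Together with P > 15 this requires P > max(15, 0.8C).
- Synopsis design text: L/C > 1.5 means P > 0.5C, and L > 15 means P > 15 − C. Together these require P > max(15 − C, 0.5C).

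Patients between the two limits qualify under the design text and fail section 5:

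| Core (mL) | Design text: penumbra above (mL) | Section 5: penumbra above (mL) |
|---|---|---|
| 10 | max(5, 5) = 5 | max(15, 8) = 15 |
| 40 | max(−25, 20) = 20 | max(15, 32) = 32 |
| 60 | max(−45, 30) = 30 | max(15, 48) = 48 |

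Under section 5 the ratio becomes the stricter of the two conditions once 0.8C > 15, that is C > 18.75 mL. Below that core volume, the penumbra minimum decides.

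**3. Example patients.**

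| Core / lesion (mL) | L/C | Penumbra (mL) | Synopsis design text | Section 5 |
|---|---|---|---|---|
| 40 / 65 | 1.63 | 25 | eligible | not eligible (ratio) |
| 10 / 20 | 2.0 | 10 | eligible | not eligible (penumbra) |
| 70 / 130 | 1.86 | 60 | not eligible (core) | eligible |

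None of the three meets section 6.1 or the synopsis inclusion list as printed. The last row arises only at a core of exactly 70 mL. Apart from that boundary, anyone eligible under section 5 is also eligible under the design text, so the disagreement runs one way.

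**The case against.** The strongest reply is that a careful reader can recover most of the intended rule. Section 5 states the ratio coherently, comes just before section 6.1 and uses the same 1.8. The two inclusion lists look like a transposition of two nouns. On the cut-off and the volume rule, three of the four places agree, and only a parenthesis in the synopsis design narrative departs. Section 7.1 sends sites to the inclusion and exclusion criteria rather than to that narrative, and one software package is named throughout. The amendment table records changes to the penumbra volume in sections 1, 5 and 6, so the narrative may be unrevised wording, although nothing confirms this.

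Much of this stands, and it limits how far the point can be pressed. Three stronger readings might be inferred and should not be.

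- **That the trial can enrol nobody.** This is true only of the printed words. Sites would probably apply the section 5 direction.
- **That many patients will later be declared ineligible and dropped under section 15.11.** The documents give no distribution of core or lesion volumes. Section 15.11 says only that an unqualified subject may be ineligible for analysis, while the synopsis and section 12.5 specify intention to treat.
- **That the treatment comparison is biased.** Mismatch is assessed before randomisation, so uneven application changes who is enrolled in both arms alike.

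What the reply does not remove is the conflict. No place is marked as controlling, and the lists to which section 7.1 points are the ones with the reversed ratio. Naming MIStar does not settle the thresholds, because its configuration is not given.

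**Conclusion.** The protocol contradicts itself on a key inclusion criterion and should be corrected. Two conflicts carry practical weight: 1.5 against 1.8 for the ratio, and perfusion lesion against penumbra for the 15 mL minimum. The reversed ratio in both inclusion lists is wrong as written, with a ceiling of about 0.82 against a required 1.8, though its meaning can be recovered from section 5. The difference between below 70 mL and at most 70 mL matters only at exactly 70 mL and is minor.

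The width of the disputed band can be calculated: penumbra from 20 to 32 mL at a core of 40 mL, for example. The share of patients within it cannot, because the protocol gives no volume distribution. The consequence is a blurred population definition, which affects to whom the result applies and possibly the size of the effect, and an eligibility rule that cannot be audited cleanly.

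The arithmetic assumes that the perfusion lesion is the sum of core and penumbra, which the text implies but does not state, and that the design-text ratio is lesion to core.

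**What to change.** Reconcile the synopsis design text, the synopsis inclusion list, section 5 and section 6.1 to a single definition repeated word for word. Write the ratio as perfusion lesion volume divided by core volume, the direction that section 5 uses and that can be satisfied. State one cut-off, one volume rule (perfusion lesion or penumbra) and one core limit. The sponsor must choose these values; this review takes no position on them. Define penumbra by formula, and confirm that the eligibility output configured in MIStar at every centre applies the same rule.

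The cost is a wording amendment, a note to sites and a check of the software settings. If recruitment has begun, the baseline volumes already recorded can be used to count patients enrolled in the disputed band. That would supply the figure the document lacks, without removing anyone from the intention-to-treat analysis.

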### 6.2 Exclusion Criteria

- Intracranial hemorrhage (ICH) or other diagnosis (e.g. tumor).
- Basilar Artery occlusion.
- Extensive early ischaemic change (hypodensity on NCCT or high signal on DWI-MRI) or early ischaemic change outside the perfusion lesion that invalidates mismatch criteria.
- Pre-stroke mRS score of  $> 2$  (indicating significant previous disability) or DBS -ve.
- Any terminal illness such that patient would not be expected to survive more than 1 year

- Any condition that, in the judgment of the investigator could impose hazards to the patient if study therapy is initiated or affect the participation of the patient in the study.
- Pregnant women.
- Other standard contraindications to thrombolysis.
- Minor stroke symptoms, or major stroke symptoms rapidly improving
- Clinical presentation suggesting subarachnoid haemorrhage
- Known bleeding diathesis and/or platelet count <100,000 or taking warfarin with INR > 1.7.
- Patients who have received heparin within 48hours must have normal aPTT.
- Major surgery or serious trauma within 14 days, serious head trauma within 3 months.
- GI or urinary tract haemorrhage within last 21 days
- Arterial puncture at a non-compressible site or lumbar puncture within 7 days
- Systolic BP > 185, diastolic BP > 110mmHg
- Clinical stroke within 3 months or history of ICH
- Known severe renal impairment (GFR < 15mls/min)

### **6.3 Other Eligibility considerations (patients taking oral anticoagulants)**

- Warfarin - thrombolysis can be used if POC INR≤1.4.or laboratory INR≤1.7
- Dabigatran – order urgent aPTT, and thrombin time. If dabigatran is known or suspected to have been taken within last 48 hours then Idarucizumab 5g IV bolus should be given prior to thrombolysis.
- Apixaban/Rivaroxaban - If Apixaban/Rivaroxaban is known to have been taken in last 12 hours then patient cannot be enrolled. If unclear, order urgent aPTT, INR, anti-Xa level: patient can be enrolled if appropriately calibrated anti-Xa level indicates <10 ng/mL apixaban or <100 ng/mL rivaroxaban.

### **6.4 Feasibility**

We are uniquely well-placed in the international stroke trials space to rapidly address this urgent knowledge gap and implement substantive changes in clinical practice. We have built an established network of collaborating hospitals across Australia, New Zealand, Taiwan, Korea, Canada, Spain, Finland, Sweden and the UK to recruit acute stroke patients into acute therapy trials. These sites have participated in a number of our trials including TASTE, EXTEND, and EXTEND-IA. Further, we now have a large network of rural/regional telestroke sites in Australia that are actively enrolling in trials such as TASTE and EXTEND-IA TNK. This is important as we expect that >50% of patients recruited in ETERNAL will be 'drip and ship', and, that the group with delays to thrombectomy may stand to gain more benefit from a more effective IV thrombolytic given prior to transfer. Recruitment is expected to take 5 years.

## 7. Study assessments and Procedures

### 7.1 Screening

Baseline physical examination will be performed on potentially eligible patients.

Multi-modal CT or MRI will be performed to assess eligibility for acute thrombolytic and thrombectomy treatment including perfusion imaging analysed with MiStar as part of standard care for stroke patients. It is expected the majority of patients will be recruited using CT.

Neurological impairment and functional scores (NIHSS, pre-stroke mRS) will be assessed by a neurologist or trained health care professional.

Bloods for standard care diagnostic evaluations will be collected and analysed.

Patients will be assessed for trial eligibility according to the Inclusion/Exclusion criteria including processing of the imaging data to assess for vessel occlusion and mismatch.

Informed consent will be obtained from patients or their authorised representative according to the Independent Ethics Committee (IEC) approved patient information and informed consent procedure and documentation which may include consent to continue participation after initial “emergency treatment to prevent serious damage to the patient’s health” in some jurisdictions.

**Imaging:** Centres will process the CT or MR images using MiStar to determine eligibility. Patients will have standardised multimodal CT or MR prior to treatment.

**Medical history, concomitant medications & ECG:** Details of patients’ medical history (including stroke history) and concomitant medications will be recorded. Results of ECG performed as part of standard care will be recorded if available.

**Blood and urine collection:** Results from standard care blood tests performed at screening will be recorded (routine haematology, biochemistry and coagulation screening tests as described in Appendix 1. Study schedule).

**Randomisation:** Patients eligible for this RCT based on imaging criteria will be randomised to ETERNAL LVO in ratio 1:1 to receive either standard of care or intravenous tenecteplase using a with covariate-adjusted randomisation procedure to minimise imbalances on the following covariates: clinician intention to give alteplase or no thrombolysis if randomised to standard of care, age, NIHSS, premorbid mRS, site of Large Vessel Occlusion (Intracranial ICA and M1 vs extracranial ICA and M2, with tandem ICA occlusions to be considered intracranial for the purpose of covariate adjustment), and onset-to-randomization time (0-4.5h, 4.5-12h, 12-24h, where wake-up stroke/uncertain onset is ‘last seen well within last 24 hours’).

## 7.2 Study Procedures

### 7.2.1 Day 0 – Treatment

**Intravenous thrombolytic treatment:** Patients will receive open-label intravenous tenecteplase at a dose of 0.25 mg/kg, given as a bolus or ‘standard of care’, which will include intravenous alteplase at the standard dose of 0.9 mg/kg up to a maximum of 90mg (10% as bolus and the remainder over 1 hour), or no thrombolytic. Randomisation will be performed as described above. The time of bolus and infusion commencement will be recorded.

Close neurological observation will be conducted primarily during the first 48 hours after treatment administration according to local clinical practice.

### 7.2.2 Day 1 (24 +/- 6 hours post treatment administration)

**Imaging:** All patients will have MRI (Including DWI, FLAIR SWI/GRE, PWI, and MRA) or, if unable to have MRI, multimodal CT (NCCT with CTA and CTP) at 24 hours post treatment to assess for reperfusion, ICH, infarct growth, and recanalisation.

For all patients who undergo thrombectomy, all DSA imaging will also be required to be uploaded to the ETERNAL eCRF.

Any additional patient imaging acquired during their hospital stay will also be required to be uploaded. Such imaging may include additional NCCT if there is an adverse event or change in neurological status.

**Clinical assessments:** Neurological assessment (NIHSS) will be performed at 24hrs by an accredited observer who is blind to acute treatment and imaging findings.

**Adverse Events:** All patients will be asked to report adverse events (refer to Section 8).

**Concomitant medications:** All concomitant medications will be recorded.

### 7.2.3 Day 90 +/- 7 days

**Clinical assessments:** As this is a PROBE (PROspective Open-label Blinded Endpoint) design trial, the primary outcome will be measured by a phone-based assessment of mRS, EQ5D and PROMIS10 from a central agency in each country. Structured questionnaires will be followed. The phone-based assessors will be blind to treatment allocation.

**Adverse events:** Adverse event data will not be collected unless for mortality, or events serious in nature. Information on stroke recurrence will be collected.

#### **7.2.4 Day 360 +/- 30 days**

**Clinical assessments:** As this is a PROBE (PRospective Open-label Blinded Endpoint) design trial, the primary outcome will be measured by a phone-based assessment of mRS, EQ5D and PROMIS10 from a central agency in each country. Structured questionnaires will be followed. The phone-based assessors will be blind to treatment allocation.

